### Sample size calculation

A total of 86 patients per group will be necessary to detect a mean difference of 0.3% and a standard deviation of 0.7% in HbA_1c_ reduction between the two treatment groups (Cohen’s *d* = 0.43), with an alpha error = 0.05 and beta = 0.2 (power = 0.8). Given an expected non-evaluable rate of 20%, a total of 216 participants will be needed, with 108 patients in each group.

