#### Exclusion criteria

Patients will be excluded if they have any of the following:Diabetes duration < 1 yearType 2 diabetes not on insulin, or on non-intensified insulin therapySevere organic disease preventing regular participation in the training coursePregnancySevere cognitive impairmentCurrent treatment of a psychiatric disorderRenal disease requiring dialysis

The treating physician will confirm that each patient satisfies the inclusion and exclusion criteria by checking the health records or by clinical assessment. Once included in the study, patients may still be excluded from the analysis if they decide to leave the study at any point for any reason, or if they miss any one treatment appointment or one of the three assessment points.

The REPLACE and IMPACT studies [1, 2] were not able to show significant improvement in glycaemic control with flash glucose monitoring vs. SMBG. Assuming that education might be able to improve the efficacy of flash glucose monitoring, exclusion of patients with previous flash glucose monitoring system use is not necessary (since the device alone does not seem to be efficacious in improving the HbA_1c_). The main objective of this study is not to prove the efficacy of flash glucose monitoring systems, but rather to evaluate the efficacy of the FLASH education and treatment programme. However, if there are substantial differences between the control and intervention groups in previous flash glucose monitoring system use, adjustment will be made during the analysis for experience of using previous flash glucose monitoring systems.

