### Content, structure and intervention of FLASH

FLASH is a structured education and treatment programme that will be delivered in a group setting, with each group comprising three to eight patients in the age range 16–75 years. This wide age range was selected so that study centres could include as many eligible patients as possible. Previous experience has shown that it is difficult to recruit homogeneous age groups. Having patients of widely differing ages is not necessarily a disadvantage, since younger people with diabetes can learn from the experiences of older ones and vice versa. If important differences are observed between the different age groups, adjustment for these factors will be made during analysis of data.

FLASH aims to empower patients by providing information and teaching strategies for better self-management of diabetes. FLASH participants are encouraged to be actively involved in their treatment: they formulate their own therapy-related goals, learn to recognise patterns in their glucose levels and to identify trends, and also to use this information for optimising daily therapy decisions. During FLASH, participants are also invited to share their experiences with flash glucose monitoring with other group members. The ultimate objective is to teach patients to live active and normal lives through efficient use of flash glucose monitoring.

FLASH uses different modern educational techniques. The guiding principle is self-management, especially self-monitoring, self-assessment, and enhancing self-treatment. Participants are provided with written material and worksheets and are encouraged to test the contents of each lesson on their own and to then discuss their experiences in the group setting. They are introduced to computer-based data analysis software and learn how to use it for optimising their own therapy. Additionally, patients define what they personally hope to achieve by attending the FLASH programme. Course instructors are provided with core content about the interpretation of flash glucose monitoring results and also optional content in slides on a secondary level if more detailed information is needed on a certain topic (e.g. exercising or hypoglycaemia).

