### Planned data analysis

Continuous data over all three time points will be summarised using descriptive statistics. Differences across the time points will be calculated for each group. The distributions of these differences will be compared using analysis of variance (ANOVA) for repeated measurements, with the FLASH group as the independent variable. If significant baseline differences are seen, the respective baseline values will be used as covariates.

Sometimes the questionnaire data may be skewed and may not fulfil the criteria for interval data. Assuming that at least rank-order data are available from the questionnaires, we will use either non-parametric tests for the evaluation of questionnaires and glucose data, or perform a transformation of the scores and glucose parameters into van der Waerden scores before applying parametric tests. Based on the data distribution and the scale of measurement, appropriate statistical methods will be selected. In the case of categorical data determined over several time points, we will use logistic regression analysis with adjustment for baseline values.

Statistical testing will be conducted at a significance level of *α* = 0.05. All analyses will be performed using SYSTAT version 12.0. For the intention-to-treat analysis missing data will be substituted by the last-observation-carried-forward method.

All data will be treated as confidential and be stored at FIDAM, the study coordination centre, for 10 years. Only FIDAM personnel will have access to the data during the study. FIDAM will monitor the flow of participants through each stage of the trial, and finally will be able to publish it.

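### Baseline HbA1c enters the primary model only if the arms differ significantly at baseline; it should be a fixed covariate, although the stated power and the overall type I error are not wrong

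*Protocol article*

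**What the plan says.** The Planned data analysis section of the protocol article forms differences across time points within each group. It compares them by repeated-measures ANOVA with FLASH group as the independent variable. Baseline values come in by a condition: "If significant baseline differences are seen, the respective baseline values will be used as covariates". No other section puts baseline HbA1c into the primary analysis unconditionally. For categorical outcomes the same section does adjust for baseline without any condition.

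Two further conditional sentences stand elsewhere:

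- Under Exclusion criteria, if previous use of a flash system differs substantially between the arms, "adjustment will be made during the analysis for experience of using previous flash glucose monitoring systems". No threshold for a substantial difference is given.
- Under Content, structure and intervention of FLASH: "If important differences are observed between the different age groups, adjustment for these factors will be made during analysis of data". This sentence is about age groups, not trial arms.

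The Sample size calculation is set "to detect a mean difference of 0.3% and a standard deviation of 0.7"% in HbA1c reduction, that is, on the SD of the change and with no covariate.

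**The concern.** In a randomised trial a baseline difference between arms is due to chance, so testing it for significance answers no useful question. The test also chooses the wrong occasions for adjustment. What matters is how far the imbalance carries over into the outcome comparison, and an imbalance just short of significance carries over almost as much as one just past it.

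A change score uses baseline only in part. If follow-up HbA1c regresses on baseline with a slope below 1, the arm that happens to start higher falls more, and that extra fall is counted as treatment effect. Including baseline as a covariate removes this and, for the same reason, usually reduces residual variance. At stake are some precision in the primary comparison and the reading of the estimate if the arms happen to be moderately imbalanced. The form of the primary model also depends on the data.

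**Working it through.** **Inputs from the article (Sample size calculation).** Difference 0.3%, SD of the HbA1c reduction 0.7%, alpha 0.05, power 0.8, 86 evaluable per group, 20% non-evaluable. Sidedness is not stated; two-sided reproduces the figure, whereas one-sided gives 68.

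**The plan's own figure.** n = 2 × (1.96 + 0.84)² × 0.7² / 0.3² = 85.5, so 86 per group. 86 / 0.8 = 107.5, so 108 per group and 216 in total. Both stated figures are reproduced. Normal-approximation power at 86 per group is 80.2%.

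**Assumptions, not in the article.** Baseline HbA1c SD (SD0) of 0.8, 1.0 or 1.3%; equal SDs at baseline and follow-up; one baseline-to-follow-up difference in place of the three-time-point model.

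**Formulas.** With equal SDs the slope of follow-up on baseline equals the correlation ρ.

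- ρ = 1 - 0.7² / (2 × SD0²)
- Residual variance with baseline as covariate, relative to the change score: (1 + ρ) / 2
- Power = Φ(0.3 / (0.7 × √((1 + ρ)/2) × √(2/86)) - 1.96), with √(2/86) = 0.1525
- Imbalance at the p = 0.05 limit: 1.96 × SD0 × 0.1525
- Shift in the unadjusted estimate there: (1 - ρ) × that imbalance

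| SD0 | ρ | Variance ratio | Power, baseline always in | Imbalance at limit | Shift | Shift / 0.3 |
|---|---|---|---|---|---|---|
| 0.8 | 0.617 | 0.809 | 87.8% | 0.24% | 0.092% | 31% |
| 1.0 | 0.755 | 0.878 | 85.1% | 0.30% | 0.073% | 24% |
| 1.3 | 0.855 | 0.928 | 83.1% | 0.39% | 0.056% | 19% |

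The largest shift goes with the smallest imbalance, because a small SD0 implies a lower slope.

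**Typical shift.** The mean absolute shift over randomisations is (1 - ρ) × SD0 × 0.1525 × √(2/π): 0.037%, 0.030% and 0.023% for the three SDs, or 8-12% of 0.3. The mean signed shift is zero.

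**Simulation of the rule** (test baseline at 0.05, adjust only if significant; 86 per group, 20,000 trials per setting). Power of the conditional rule against always adjusting was 80.7% and 87.2% (SD0 0.8), 80.5% and 84.5% (1.0), 79.9% and 82.7% (1.3). In a separate simulation of 100,000 trials per setting, with ρ of 0.5, 0.7 and 0.8, the baseline test was significant in about 5% of trials. The rule's overall type I error was 0.043 to 0.048.

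**Without equal SDs.** Let b be the slope. Residual variance is 0.49 - (1 - b)² × SD0². With SD0 = 1.0 and b = 0.9 this is 0.48 (follow-up SD about 1.14). Power is then 81.0%, and the shift at the limit is 0.1 × 0.30 = 0.03%. With b = 1 there is neither gain nor shift.

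**The case against.** The best case for the plan is that nothing it promises fails. The sample size uses the SD of the change and assumes no covariate. The conditional rule still delivers about 80% power, and overall type I error stays at or slightly below 5%. A reader might infer from the conditional rule that the trial is underpowered or that its false-positive rate is inflated. The calculations support neither; what is lost is an efficiency gain that was available.

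A reader might also take the 19-31% shift as a bias in the trial's result. It is not. It applies only at an imbalance just below the cut-off, the typical shift is well under half of that, and it averages to zero over randomisations. The objection that the figures need equal SDs also stands: entry is restricted on baseline HbA1c (7.5-14%), so equality is not assured. A smaller follow-up SD would make the gain larger, and a larger one would make it smaller.

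A third tempting reading puts all three conditional sentences together as triggers based on arm imbalance, each wasting power. The age sentence refers to differences between age groups, so the argument about testing randomised baselines does not reach it; only its undefined threshold can be criticised. For previous flash use the trigger is arm imbalance, but the article gives no prognostic strength for it or for age, so no gain from either can be calculated.

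One defence does not stand: that covariate choice is left to an unseen analysis plan. The article states a rule, and the rule is the problem.

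**Conclusion.** The point holds for baseline HbA1c. The article ties baseline adjustment of the primary outcome to a significance test that fires in about 5% of randomised trials, so the usual result would be an unadjusted change comparison. Fixing the adjustment in advance would lift power from 80% to about 83-88% and remove a conditional shift of 0.06-0.09% HbA1c at the cut-off. These sizes rest on a baseline SD of 0.8-1.3% and equal SDs over time, neither of which is in the article, and they shrink towards nil as the slope approaches 1. This is a worthwhile improvement at no cost, not an error in the stated power or in type I error control. For previous flash use the point is one of pre-specification only.

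**What to change.** Delete the sentence that makes baseline adjustment depend on a significant difference. State instead that the primary model always includes baseline HbA1c as a continuous covariate, whatever balance is observed. Apply the same rule, with the outcome's own baseline value, to continuous secondary outcomes that have a baseline value and are analysed parametrically. It cannot apply to satisfaction with FLASH, which is asked only of the intervention group at the end of the programme. Categorical outcomes need no change.

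Decide before the groups are compared whether previous flash use is a covariate, and drop the observed-difference trigger. For age, either name it as a covariate in advance or say what the age-group sentence is meant to do.

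The cost is wording only. Baseline HbA1c and age are already collected, adjustment for previous use is already contemplated, and the sample size can stay as it is.

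### For questionnaire and glucose outcomes the test is chosen from the observed data without a stated rule, and baseline adjustment is only conditional; one baseline-adjusted method should be named in advance

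*Protocol article*

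**What the plan says.** All of the relevant text is in the protocol article, section Planned data analysis.

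- Continuous data are compared through differences between time points, by repeated-measures ANOVA with group as the factor. On baseline it says: "If significant baseline differences are seen, the respective baseline values will be used as covariates".
- For questionnaires and sensor glucose data there are two routes. The first is "we will use either non-parametric tests for the evaluation of questionnaires and glucose data"; the alternative is to "perform a transformation of the scores and glucose parameters into van der Waerden scores before applying parametric tests".
- The choice is then left open: "Based on the data distribution and the scale of measurement, appropriate statistical methods will be selected".

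The section does not name the non-parametric test, say whether it is applied to change or to the follow-up value, or call either route adjusted or unadjusted. It gives no threshold for choosing, no time at which the choice is made, and no statement that whoever chooses is blind to group. Repeated categorical outcomes, by contrast, are adjusted for baseline without any condition.

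The Sample size calculation section concerns HbA1c only. No power, effect size or baseline–follow-up correlation is given for any questionnaire or glucose outcome.

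**The concern.** The either/or covers nearly all the secondary evidence: time in glycaemic ranges, glucose variability and the questionnaire scores compared between groups. Scale of measurement is known before any data arrive, so what can actually trigger the choice is the observed distribution. A choice made outcome by outcome, with no rule, can drift towards the more favourable result, and nothing in the text prevents that.

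The baseline condition is a second dependence on the data, and it uses the wrong trigger. In a randomised comparison, the reason to adjust for a baseline score is that it predicts the follow-up score. Whether the groups happen to differ significantly at baseline says little about that. Under the stated rule most outcomes would go unadjusted, although the baseline score is collected anyway. Two things are therefore at stake: a possible rise in false positives, and avoidable loss of power for secondary outcomes.

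**Working it through.** **1. The plan's own sample size.** Inputs: "A total of 86 patients per group will be necessary to detect a mean difference of 0.3% and a standard deviation of 0.7"%, "with an alpha error = 0.05 and beta = 0.2 (power = 0.8"). With a two-sided test, n per group = 2 × (1.960 + 0.842)² × (0.7/0.3)² = 85.5, so 86. Allowing for 20% non-evaluable: 86/0.8 = 107.5, so 108 per group and 216 in total. This agrees with the plan. Only the 86 per arm is carried forward; the HbA1c effect size is not borrowed for the secondary outcomes.

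**2. False positives.** Simulation under no effect, nominal 5%, 86 per arm, 20,000 runs per setting, normal and skewed outcomes, assumed baseline–follow-up correlation r = 0.3, 0.5, 0.7 and 0.8:

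| How the test is chosen | Rejection rate |
|---|---|
| Each test fixed in advance | 4.6–5.3% |
| Chosen by a skewness test on pooled data, ignoring group | 4.7–5.3% |
| Smaller p-value of rank test and van der Waerden t test, treated alike | 5.5–6.2% |
| Smaller p-value of unadjusted rank test and baseline-adjusted van der Waerden analysis | 6.5–8.7% |

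The last two rows assume that the choice follows the result. Allowing for variation between simulations, they support about 5–6.5% and at most about 8–9%.

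**3. Power.** Assumptions not in the protocol: a shift of 0.35 SD, equal SD at baseline and follow-up, and r from 0.3 to 0.8. The input from the protocol is 86 per arm. On the normal scale, power = Φ(λ − 1.96), with 0.35 × √(86/2) = 2.295 and

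- rank test on change: λ = 2.295 × √(3/π) / √(2(1 − r)), where √(3/π) = 0.977;
- van der Waerden t test on change, unadjusted: λ = 2.295 / √(2(1 − r));
- van der Waerden scores with baseline as covariate: λ = 2.295 / √(1 − r²).

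For r = 0.5 these are λ = 2.243, 2.295 and 2.650.

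| r | Rank test on change | van der Waerden on change | van der Waerden, baseline-adjusted | Adjusted minus rank test |
|---|---|---|---|---|
| 0.3 | 47.4% | 49.2% | 67.2% | 19.8 points |
| 0.5 | 61.1% | 63.1% | 75.5% | 14.4 points |
| 0.6 | 70.8% | 72.8% | 81.8% | 11.0 points |
| 0.7 | 82.5% | 84.2% | 89.5% | 7.0 points |
| 0.8 | 94.4% | 95.2% | 96.9% | 2.5 points |

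Treated alike, the two named options differ by 0.9 to 2.0 points. The rest of the gap, 1.6 to 18.0 points, comes from the baseline covariate. A simulation with 86 per arm and r = 0.6 gave 72% for the rank test on change and 82% for the adjusted analysis on normal data (68% and 80% on skewed data), in line with the table.

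**The case against.** The strongest reply is that the selection sentence refers to distribution and scale, not to group results. Read as a choice from the pooled distribution, it costs nothing in false positives. That is correct, and it limits the point: the text permits this reading but does not require it.

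A reader might infer that one of the plan's two options is an unadjusted test that loses about 10 points of power against the other. The documents do not support this. Neither option is labelled adjusted or unadjusted, the baseline condition is stated without exempting either route, and treated alike they are within about 2 points. A gap of about 10 points needs both a difference in adjustment and a particular correlation, which the protocol does not give.

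A reader might also infer that the error rate is uncontrolled, or reaches 9–10%. That figure needs a third test, on the follow-up value, to be added to the choice and the best result picked; the comparison the section describes for continuous data is of changes.

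Finally, this is a journal article, and an unseen analysis plan may settle the test. That holds for missing detail. It does not remove the stated rule that adjusts only after a significant baseline difference, nor the stated choice from the data.

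**Conclusion.** The point holds as a limited one. The protocol leaves the method for questionnaire and glucose outcomes to the observed data without a criterion or a group-blind rule, and makes baseline adjustment depend on a significance test.

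The false-positive risk is modest and arises only if the choice is informed by the group comparison. The firmer loss is in power, and it comes from omitting the covariate rather than from choosing between ranks and van der Waerden scores. Its size rests on the assumed 0.35 SD shift and on the unknown correlation: small at 0.8, large at 0.3. As no power target is stated for these outcomes, none is missed.

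HbA1c, the primary outcome, falls under the ANOVA sentence, so this selection step does not touch the main hypothesis test. The calculations used continuous outcomes; heavily tied ordinal scores were not simulated.

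**What to change.** Replace the either/or and the selection sentence with one rule, fixed before group results are seen:

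- For every questionnaire and glucose outcome measured at baseline in both groups, transform to van der Waerden scores and compare groups with the baseline score always a covariate, at each post-baseline time point the plan already analyses (t1 where measured, and t2).
- Report raw-scale group differences alongside.
- Keep rank tests as sensitivity analyses.
- Scales given only to the intervention group (satisfaction with FLASH, fidelity) have no control comparison and stay descriptive.

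The transformation is already named in the plan and the baseline scores are already collected, so no further patients or data are needed. It is still a change of analysis: adjustment becomes unconditional. The downside is that the test is on a transformed scale, which is why the raw differences must stand next to it.

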## Discussion

For quality of reporting, all standard protocol items recommended for international trials were taken in consideration according to the SPIRIT (Standard Protocol Items: Recommendations for Interventional Trials) Checklist, providing recommendations for a minimum set of ethical, scientific, and administrative elements which should be addressed in a clinical protocol [19] (see Additional file 1).

Patient enrolment will take place during the summer break and vacation periods and may be at different times at different centres.

The main results will be presented in conferences and reported in peer-reviewed publications. If FLASH is found to be beneficial the programme will be certified in Germany, so at the end every concerned patient will benefit.

### Trial status

Protocol version number: 02.01.2018_1 (4 January 2018).

The study is currently (at the time of submission) recruiting participants. This can be seen at ClinicalTrials.gov (NCT03175315). Patient recruitment started on 2 May 2017, and will be completed by early October 2017. The first results are expected to be available in 2018.

## Abbreviations

AGP: Ambulatory glucose profile
CDE: Certificated diabetes educators
CES-D: Centre for Epidemiologic Studies Depression Scale
CRF: Case Report Form
DAS: Diabetes Acceptance Scale
DDS: Diabetes Distress Scale
eCRF: Electronic Case Report Form
EQ-5D: Health-oriented Quality of Life – German version
FIDAM: Research Institute of Diabetes Mergentheim
FLASH: Name of the new patient education and treatment programme
GMAT: Glucose Monitoring Assessment Tool
GMSS: Glucose Monitoring Satisfaction Survey
HbA_1c_: Glycated haemoglobin A
HFS: Hypoglycaemia Fear Survey
HPLC: High-performance liquid chromatography
PAID: Problem Areas In Diabetes
PHQ-8: Personal Health Questionnaire
RCT: Randomised controlled trail
SMBG: Self-monitoring blood glucose
SPIRIT: Standard Protocol Items: Recommendations for Interventional Trials
SYSTAT: Statistical software, San Jose, CA, USA
WHO-5: World Health Organisation Well-being Index
